Providing immediate front-line protection against rapidly dividing bacterial and fungal infections, neutrophils are critical effector cells of the innate immune system. Severe thermal injury has been shown to lead to impairments in a range of neutrophil functions such as chemotaxis,^15–17^ phagocytosis,^17–19^ generation of reactive oxygen species^18 19^ and the formation of neutrophil extracellular traps, which contribute to circulating cell-free DNA (cfDNA).^18^ Given their critical role in the elimination of bacterial infections, this postburn reduction in neutrophil function has been proposed to underlie the increased susceptibility of thermally injured patients to nosocomial infection and sepsis. Interestingly, results from a number of recent longitudinal studies suggest that an early assessment of the phenotype and/or function of the circulating neutrophil pool can be used to predict, diagnose and/or monitor postburn sepsis.^15 18 20^ In a cohort of 13 patients with major burns, Jones *et al* demonstrated that neutrophils isolated from patients during a septic episode displayed a spontaneous migratory phenotype that was significantly different to that recorded for neutrophils isolated from burns patients with or without SIRS.^15^ Importantly, demonstrating both its prognostic utility and monitoring potential, this phenotype was also observed in patients prior to sepsis diagnosis and was corrected following effective antibiotic treatment.^15^ Extending these observations, we recently demonstrated, in a cohort of adult burns patients, that a combined measure of neutrophil phagocytic capacity, immature granulocyte (IG) count and plasma cfDNA levels exhibited strong discriminatory power (area under receiver operating characteristic, AUROC 0.935) on day 1 of injury for distinguishing between patients who did or did not develop sepsis.^18^ Moreover, we found that a statistical model that combined the variables of neutrophil phagocytosis and IG count with a clinical scoring metric (revised Baux score) provided discriminatory power (AUROC 0.986) that was greater than any variable alone.^18^ Although highlighting the potential utility of combined clinical and immune biomarker data for the early prediction of sepsis, our original study was designed to be exploratory and hypothesis generating in nature rather than confirmatory, and as such lacked a formal power calculation. Moreover, the study was limited by its small sample size, single-centre design and the inclusion of data only from adult burns patients. Thus, a much larger study that prospectively validates this novel suite of biomarkers in both adult and paediatric burns patients is required.

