### Sample size

The sample size for this study is based on data collected from adult patients recruited into the SIFTI-1 study.^18^ Of the 57 adult burns patients who survived for at least 7 days following study enrolment, 35 developed sepsis, equating to a prevalence of 61%. Of these, 33 patients, with a TBSA burn ≥15%, had measurements of neutrophil phagocytic capacity, plasma cfDNA levels and IG count recorded on day 1 of injury. These data provided good discriminatory power to identify septic patients, with logistic regression modelling providing an area under the ROC of 0.935. Adjusted for shrinkage following internal bootstrap model validation to account for potential overfitting, this model exhibited a specificity of 0.75 and a sensitivity of 1.00. Based on this information, we computed the sample sizes required to estimate a 95% CI for sensitivity (with a maximum width of 10%) and for specificity (with a maximum width of 20%) for prevalence rates of sepsis ranging from 50% to 70%. Assuming a prevalence of sepsis of at least 60% and that the ‘true’ sensitivity is at least 90% and the ‘true’ specificity is at least 70%, these analyses revealed a total of 220 patients would allow us to reliably rule out a sensitivity less than 84% and a specificity of less than 59%. Assuming that the 10% drop-out rate we recorded for patients over the first 7 days of the SIFTI-1 study holds true for this follow-on study, then a total sample size of 245 burns patients, which includes both adult and paediatric age groups, is required for the SIFTI-2 study.

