### Data analysis

Data will be assessed for normality using the Shapiro-Wilk test. Normally distributed data will be presented as mean values with SD. Non-normally distributed data will be presented as median values with IQR. Comparisons of baseline continuous data (eg, demographics, injury characteristics) between two groups (eg, HCs vs burns patients or septic vs non-septic patients) will be conducted using an unpaired Student’s t-test for normally distributed data or the Mann-Whitney U test for non-normally distributed data. Categorical baseline data will be compared using a χ^2^ test. Laboratory data obtained from HCs and patients across the different sampling time points will be compared using either a one-way analysis of variance with a Dunnett post hoc test for normally distributed data or a Kruskal-Wallis test with a Dunns post hoc test for non-normally distributed data. A p <0.05 will be considered statistically significant.

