We will determine in how many participants the measurements of neutrophil phagocytic capacity, plasma cfDNA levels and IG count on day 1 of injury predicted a diagnosis of sepsis. This proportion will be reported along with 95% CIs calculated by binomial exact methods. The accuracy of this day 1 biomarker model will be determined through standard estimates of sensitivity, specificity, predictive values and likelihood ratios, with 95% CIs. We will investigate the value added by this day 1 biomarker test when compared with information obtained from other potentially informative sets of biomarkers (eg, revised Baux score). These combinations of tests will be assessed using logistic regression models. Using multivariable logistic regression analysis, we will also generate predictive probabilities for various combinations of these candidate biomarkers. This logistic modelling will aim to derive a prognostic regression function (ie, probability of sepsis) using the day 1 values of each candidate biomarker and other demographic or burn-related variables. Models of varying complexity may be compared through ROC analyses. Longitudinal data collection will enable us to examine how the performance of these models change over time. Limitations associated with the logistic regression approach lie mainly in its generalisability to other data sets. Thus, techniques such as bootstrapping to enhance generalisability will be applied for model validation. In sensitivity analyses, missing data will be estimated by multiple imputation and maximum-likelihood methods, as appropriate, in order to explore the potential bias and reduced statistical power associated with listwise deletion.

Serial sampling will allow for repeated measures analyses of our candidate biomarkers, enabling us to model their kinetics over time and examine how this differs between septic and non-septic patients. For the analysis of longitudinal data, continuous outcomes will be analysed using linear regression to compare the septic and non-septic groups, with mean differences and 95% CIs reported. For other outcomes, analysis of daily measurements will be performed using generalised linear mixed models to account for the hierarchical structure of the data. Summaries of model output will be provided with model effects presented both as estimates with associated 95% CIs and also, where appropriate, as plots to visualise the time course of fitted outcomes.

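### Added value over the revised Baux score: the only model comparison named is an optional ROC analysis, which is a poor test for nested models; a likelihood-ratio test should be stated

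*Protocol article*

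**What the plan says.** All of this is in the Data analysis section of the protocol article unless stated otherwise.

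- The question: "We will investigate the value added by this day 1 biomarker test when compared with information obtained from other potentially informative sets of biomarkers", with the revised Baux score as the example.
- The method attached to it: "These combinations of tests will be assessed using logistic regression models".
- The models are built in this cohort: "This logistic modelling will aim to derive a prognostic regression function".
- The comparison of models: "Models of varying complexity may be compared through ROC analyses". The wording is permissive, and no other method of comparing models is named.
- Internal validation: "techniques such as bootstrapping to enhance generalisability will be applied for model validation". Whether this extends to the ROC comparison is not stated.
- The significance level: "A p <0.05 will be considered statistically significant".

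The Introduction reports that, in the earlier study, a model of phagocytosis, IG count and revised Baux score "provided discriminatory power (AUROC 0.986) that was greater than any variable alone".

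**The concern.** Baux alone and Baux plus phagocytic capacity, IG count and cfDNA are nested logistic models. The added-value null is that the three biomarker coefficients are zero given Baux. A ROC comparison can be carried out in two ways, and neither addresses that null well.

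- **By size of AUROC.** Extra fitted terms nearly always raise the apparent AUROC in the patients used for fitting, whether or not they carry information.
- **By a paired test of the two AUROCs.** The usual normal reference treats the two scores as fixed. Under the added-value null the two fitted scores converge to the same score, the reference fails, and the test becomes very conservative.

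The Baux score needs no laboratory assay, so whether the biomarkers improve on it bears directly on their usefulness. A study meant to validate should not leave that answer to a comparison that noise can win or that misses a modest real gain.

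**Working it through.** **Inputs from the article (Sample size).** 220 evaluable patients, sepsis prevalence 60%, sensitivity 90%, specificity 70%, dropout 10%. Three biomarkers are added to one clinical score.

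**The plan's own figures first.** Septic: 0.60 × 220 = 132. Non-septic: 220 − 132 = 88. Exact (Clopper-Pearson) lower 95% limits are 83.6% for 0.90 of 132 and 59.3% for 0.70 of 88. Wilson gives 83.7% and 59.8%. These agree with the lower limits of 84% and 59% given under Sample size. 220 / 0.90 = 244.4, rounded up to 245. The sample size reproduces and is not in question.

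**Assumptions not in the article.** Predictors are independent standard normal. The Baux-only AUROC is not given, so it was varied over about 0.64-0.90. Biomarker effects are log-odds per SD, equal for the three markers.

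**Quantities computed in each simulated data set (N = 220, about 60% sepsis).**

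1. Apparent change: ΔA = AUROC(Baux + 3) − AUROC(Baux), both evaluated in the patients used for fitting.
2. Paired test: z = ΔA / SE(ΔA), with the DeLong SE; reject if |z| > 1.96.
3. Likelihood-ratio test: G = 2 × [logL(Baux + 3) − logL(Baux)]; reject if G exceeds the 95% point of chi-square on 3 df.
4. Optimism-corrected change: ΔA − (O_full − O_Baux). O is the mean, over bootstrap resamples, of a refitted model's AUROC in the resample minus its AUROC in the original data.

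**No added value (all three coefficients zero).**

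| Quantity | Share of data sets |
|---|---|
| Apparent AUROC higher with the markers | about 93% |
| Optimism-corrected AUROC higher | about 18-23% |
| Paired AUROC test rejects (nominal 5%) | about 0.2-1.2% |
| Likelihood-ratio test rejects (nominal 5%) | about 5-7% |

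The mean apparent rise is small, 0.004 to 0.016, but it is nearly always positive.

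**Real added value.** AUROCs are those of Baux alone and of the full model.

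| Log-odds per SD | AUROC | Likelihood-ratio power | Paired-test power | Gap (points) |
|---|---|---|---|---|
| 0.3 | 0.78 to 0.80 | 77% | 34% | 43 |
| 0.3 | 0.84 to 0.85 | 72% | 24% | 48 |
| 0.3 | 0.89 to 0.90 | 59% | 19% | 40 |
| 0.4 | 0.83 to 0.86 | 93% | 55% | 38 |
| 0.6 | 0.76 to 0.83 | 100% | 97% | 3 |
| 1.0 | 0.84 to 0.92 | 100% | 100% | 0 |
| 1.5 | 0.79 to 0.94 | 100% | 100% | 0 |

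Across the runs with small to moderate effects the gap was roughly 20 to 48 points. It closes as the effect grows.

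**The case against.** The strongest reply is that the article does not commit to what is criticised, and much of that stands.

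- A reader might infer that added value will be decided by which model has the higher AUROC. The text does not say so. The ROC comparison is optional, and the added-value question is assigned to logistic regression models, within which a nested test is available.
- A reader might infer that a paired test of AUROCs is planned. None is named, so the conservative error rate and the power loss apply only if one were chosen.
- The 93% applies to uncorrected AUROCs. Bootstrapping is planned, and under Sample size the team describes adjusting its earlier model for shrinkage by bootstrap. If AUROCs are corrected in this way, the false rise falls to about 18-23%. That is a large improvement, but still not a test at 5%.
- The Introduction's 0.986 might be read as showing that the earlier study settled added value by AUROC size. It compares two biomarkers plus Baux with single variables, not Baux with Baux plus three biomarkers, and does not say how added value was decided.
- Some comparisons, such as biomarkers alone against Baux alone, are not nested. The likelihood-ratio test does not apply there and ROC comparison is a standard tool.
- The power gap depends on assumed effects. The article's only effect figures are AUROCs of 0.935 and 0.986, and near such values the gap vanishes.
- The analysis plan is not shown and may already name a test.

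What remains is that the article poses a nested question and the one comparison it names is ill-suited to answering it.

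**Conclusion.** The point holds as a limited, wording-level improvement. ROC analysis is the only named way to compare models of differing complexity. For Baux against Baux plus three biomarkers in the same patients, it is a poor test of added value. Compared by size without correction, it favours three useless markers about 93% of the time. Tested by a paired method, it would be very conservative and would lose roughly 20 to 48 points of power for small to moderate effects. The second statement is conditional on a test the article does not name, and the loss disappears for large effects. All of these figures rest on independent normal markers and an assumed Baux-only AUROC of about 0.64-0.90.

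It does not follow that the validation itself is unsound. The accuracy estimates with confidence intervals, and the 220 and 245 patients, do not depend on this comparison.

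**What to change.** State in Data analysis that:

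- added value over the revised Baux score will be tested by the likelihood-ratio test on 3 df, comparing Baux plus phagocytic capacity, IG count and cfDNA with Baux alone, both fitted to the same patients;
- the change in AUROC will be reported as a descriptive effect size with a 95% CI, corrected for optimism by refitting both models in each bootstrap resample;
- ROC comparison, also optimism-corrected, is kept for non-nested models such as biomarkers alone against Baux alone.

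If the analysis plan already says this, the article need only be aligned with it. The cost is wording only, because the logistic models and the bootstrapping are already planned. The small downside is that the corrected AUROC gain will look smaller than the apparent one.

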**Methods and analysis:**

This multicentre, longitudinal, observational cohort study will enrol 245 paediatric and adult patients with moderate to severe burns within 24 hours of injury. Blood samples will be obtained at 19 postinjury time points (days 1–14, day 28, months 3, 6, 12 and 24) and analysed for neutrophil phagocytic activity, IG count and cfDNA levels. Patients will be screened daily for sepsis using the 2007 American Burn Association diagnostic criteria for sepsis. In addition, daily multiple organ dysfunction syndrome and Sequential Organ Failure Assessment Scores will be recorded relationships between neutrophil phagocytic activity, IG count and plasma cfDNA levels on day 1 of injury and the development of sepsis will be examined using logistic regression models.

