Characterised by elevated circulating concentrations of proinflammatory cytokines and immune activation, severe thermal injury results in a systemic inflammatory response syndrome (SIRS).^8^ This immediate and persistent inflammatory and hypermetabolic state triggers a physiological response in burns patients that mirrors that observed in patients with sepsis. Indeed, fever, tachycardia and tachypnoea, which were included by the American Burn Association (ABA) in their latest criteria for diagnosing sepsis among hospitalised burns patients,^9^ are examples of some of the clinical manifestations used to identify patients with SIRS.^10^ Thus, in response to a sterile insult, burns patients exhibit many of the classic diagnostic biomarkers of sepsis, thereby making the diagnosis of this secondary complication extremely difficult. Faced with this clinical challenge, a number of studies have searched for prognostic and diagnostic biomarkers of postburn sepsis. To date, a number of potential candidates, which include procalcitonin, tumour necrosis factor-alpha, interleukin (IL)-6 and IL-8, have been identified.^11^ However, as with clinical parameters, these markers of inflammation are elevated during the initial SIRS response triggered by sterile burn injury,^8^ which may explain why statistical models built on these biomarkers to predict postburn sepsis in children and adults exhibit poor sensitivity and specificity.^12 13^ Given that for every hour delay in the treatment of sepsis, the risk of death increases by 4%,^14^ there is an urgent need to identify novel biomarkers that can be used to accurately predict sepsis in thermally injured patients.

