### Data collection and patient outcomes

In this prospective longitudinal study, data will be acquired from burns patients at the following 19 postinjury time points: days 1–14, day 28 (±3 days) and months 3, 6, 12 and 24 (±2 weeks). Patient enrolment into the study began on 27 November 2016, with an estimated end date of December 2025.

Across the settings of paediatric and adult burns, a significant number of studies have undertaken serial blood sampling to investigate the short (<1–7 days), medium (8–34 days) and long (35–1100 days)-term inflammatory response to thermal injury and its relationship with patient outcome.^22–28^ In contrast, very little data currently exist on the acute and long-term effects of thermal injury on the immune system.^19 24 29^ Thus, generating data on the kinetics of the immune response to burn injury via serial sampling in both our adult and paediatric cohorts will allow us to not only establish how long burn-induced changes in immunity persist for, when compared with HCs, but also compare the immune response of septic and non-septic burns patients over time. Generating and interrogating such novel data may provide mechanistic insights into the long-term health complications reported by survivors of burn trauma, which include an increased susceptibility to respiratory infections.^30^

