#### Demographic and physiological data

Within 24 hours of injury, information on patient demographics, injury characteristics and baseline physiological data will be collected and recorded in paper and electronic CRFs. At subsequent study time points, physiological data will be collected and recorded in the electronic CRF. Table 1 summarises the data that will be recorded for all patients.

**Table 1 T1:** Demographic and clinical data that will be recorded in patient case report forms following enrolment into the SIFTI-2 study

Day 1 (within 24 hours of injury)			Days 2–14	Day 28, months 3, 6, 12, 24
Demographic data	Injury characteristics	Physiological data	Physiological data	Physiological data
Age Sex Ethnicity Time from injury to arrival at burn centre Medical comorbidities History of alcohol or substance misuse	% TBSA % Body surface area full thickness burn Burn mechanism Presence of inhalation injury and severity ABSI APACHE II AIS ISS NISS PIMS-2 Revised Baux score GCS score	Heart rate (bpm) Blood pressure (mm Hg) Mean arterial pressure (mm Hg) Oxygen saturation (%) Respiratory rate (breaths/minute) Temperature (^o^C) Blood glucose (mMol/L) Height (m) Weight (kg) BMI (kg/m^2^)	Heart rate (bpm) Blood pressure (mm Hg) Mean arterial pressure (mm Hg) Oxygen saturation (%) Respiratory rate (breaths/minute) Temperature (^o^C) Blood glucose (mMol/L) Height (m) Weight (kg) BMI (kg/m^2^) Mode of ventilation Early Warning Score Use of haemofiltration or dialysis Date of discharge/Date of death	Heart rate (bpm) Blood pressure (mm Hg) Mean arterial pressure (mm Hg) Oxygen saturation (%) Respiratory rate (breaths/minute) Temperature (^o^C) Blood glucose (mMol/L) Height (m) Weight (kg) BMI (kg/m^2^)

PIMS-2 scores will be calculated for children<16 years. % TBSA will be calculated using the Lund and Browder chart.

ABSI, Abbreviated Burn Severity Index; AIS, Abbreviated Injury Scale; BMI, body mass index; GCS, Glasgow Coma Scale; APACHE II, Acute Physiology And Chronic Health Evaluation II; ISS, Injury Severity Score; NISS, New Injury Severity Score; PIMS-2, Paediatric Index of Mortality Score-2; SIFTI-2, Scientific Investigation of the Biological Pathways Following Thermal Injury-2; TBSA, total body surface area.

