#### Outcomes

In line with our original study,^18^ sepsis will be defined according to the 2007 ABA diagnostic criteria for sepsis in burns.^9^ A diagnosis of sepsis will be made when >3 of the following criteria are met along with a positive bacterial culture or when a clinical response to antibiotics is detected:

Temperature (>39^°^C or<36^°^C).Progressive tachycardia (adults, >110 beats per minute; children, >2 SD above age-specific norms (85% of age-adjusted maximum heart rate)).Progressive tachypnoea (adults, >25 breaths per minute not ventilated or minute ventilation >12 L/minute for ventilated patients; children, 2 SD above age specific norms (85% of age-adjusted maximum respiratory rate)).Thrombocytopenia (Adults, platelet count <150x10^9^/L (this will not be applied until 3 days after initial resuscitation; children, <2 SD below age-specific norms).Hyperglycaemia (untreated plasma glucose >200 mg/dL or insulin resistance as defined by either (1) >7 units of intravenous insulin per hour or (2) significant resistance to insulin (>25% increase in insulin requirements over 24 hours).Feed intolerance (inability to continue enteral feeding >24 hours defined using (1) abdominal distension, (2) enteral feeding intolerance (adults, two times the feeding rate; children, residual >150 mL/hour) or (3) uncontrollable diarrhoea (>2500 mL/day for adults or >400 mL/day in children).

Blood cultures will be taken whenever the temperature of a patient is >38.5°C and they will be acquired from a clean venepuncture site where possible using a sterile technique. If such a site is not accessible, due to the patients injuries, then blood cultures will be obtained from a pre-existing central venous catheter. The results will be interpreted following detailed discussions with the microbiology team.

Burn wound infection/sepsis will be documented in the CRF after assessment by a senior surgeon together with information attained from the relevant microbiology wound swabs/tissue biopsies. In addition, time to 95% wound healing will be documented as an overall measure of the patients care and for wound related complications such as wound sepsis.

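### Later-day model performance and the septic versus non-septic curves use sepsis as a grouping without onset time, so prediction is mixed with detection of sepsis already present

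*Protocol article*

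**What the plan says.** In the Data analysis section, the prognostic function is a logistic model for the probability of sepsis, built "using the day 1 values of each candidate biomarker and other demographic or burn-related variables". The same paragraph adds: "Longitudinal data collection will enable us to examine how the performance of these models change over time". The next paragraph turns to repeated measures. It proposes to model biomarker kinetics and how they differ by sepsis status, and states that "continuous outcomes will be analysed using linear regression to compare the septic and non-septic groups".

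The Outcomes section defines sepsis as more than three listed criteria plus a positive culture or a clinical response to antibiotics. It gives no period within which sepsis must occur, and no analysis uses the date of onset.

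On ascertainment, the Abstract says: "Patients will be screened daily for sepsis using the 2007 American Burn Association diagnostic criteria for sepsis", with no end day. The Outcomes section says: "Blood cultures will be taken whenever the temperature of a patient is >38.5°C", also with no end day. The section on data collection and patient outcomes says "data will be acquired from burns patients at the following 19 postinjury time points: days 1–14, day 28 (±3 days"), followed by months 3, 6, 12 and 24. The section on demographic and physiological data says "Table 1 summarises the data that will be recorded for all patients". That table has columns for day 1, for days 2 to 14, and for day 28 with the later months. Neither schedule contains anything for days 15 to 27.

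**The concern.** The study sets out to validate early prognostic biomarkers. A marker measured on day 7 is prognostic only for patients who are not yet septic on day 7. If the outcome is whether the patient is ever septic, a patient diagnosed on day 4 and still septic on day 7 enters the day 7 sensitivity as a success, although nothing was predicted. The share of such patients can only grow with the sampling day. The test could therefore seem to improve over time merely because more of the cases are already ill.

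The kinetic comparison has the same weakness. A septic patient's samples from before, during and after sepsis all fall in one group. The Introduction itself cites a 13-patient cohort in which a neutrophil migration phenotype was present during sepsis, was also seen before diagnosis, and resolved after effective antibiotic treatment. Migration is not one of the three markers under validation here. It does show, however, that a neutrophil measure can move with the phase of sepsis, and a pooled group mean cannot display that.

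A separate matter is the period of ascertainment. The day 1 sensitivity and specificity have denominators that depend on how long sepsis is looked for, and the article gives two descriptions of that period that do not match.

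**Working it through.** **1. The plan's own figures.** The Sample size section has 220 evaluable patients and 10% drop-out: 220 / 0.9 = 244.4, rounded up to 245, as stated. At 60% prevalence, 220 × 0.60 = 132 septic and 88 non-septic patients. With sensitivity 0.90 and specificity 0.70, the lower exact 95% limits are 83.6% and 59.3%, which agree with the stated 84% and 59%. This point disputes none of these figures. They supply the 132 cases used below.

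**2. What scoring against an ever/never label does.** Let g be the share of ever-septic patients already septic at the sample, s1 the sensitivity in established sepsis and s2 the sensitivity for sepsis still to come. Then

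apparent sensitivity = g × s1 + (1 − g) × s2

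The documents give none of g, s1 or s2. I assume s1 = 0.95 and vary the other two. For example, g = 0.50 and s2 = 0.70 give 0.475 + 0.350 = 0.825.

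| g | Already septic | Incident cases | Apparent, s2 = 0.50 | Apparent, s2 = 0.70 | Apparent, s2 = 0.90 | Exact 95% CI width, incident cases only, sensitivity 0.90 |
|---|---|---|---|---|---|---|
| 25% | 33 | 99 | 0.61 | 0.76 | 0.91 | 13 points |
| 50% | 66 | 66 | 0.73 | 0.83 | 0.93 | 16 points |
| 75% | 99 | 33 | 0.84 | 0.89 | 0.94 | 23 points |
| 90% | 119 | 13 | 0.91 | 0.93 | 0.95 | 38 points |

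The overstatement runs from about 1 point (g = 25%, s2 = 0.90) to about 40 points (g = 90%, s2 = 0.50). It is small when the marker predicts nearly as well as it detects, and large when it does not. The last column is the price of the correction. With all 132 cases the same interval is 11 points wide.

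**3. The same effect on AUROC.** For a normally distributed marker with separation d, AUROC = Φ(d/√2). Assumed separations of 1.0 SD before onset and 2.5 SD after onset give 0.760 and 0.961. With half the cases already septic, the apparent AUROC is 0.5 × 0.760 + 0.5 × 0.961 = 0.861, against a predictive value of 0.760. This is one assumed setting and shows direction only.

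**4. The ascertainment period, side by side.** The Abstract's daily screening and the Outcomes section's culture trigger are open-ended. The data schedule and Table 1 are daily to day 14 and then jump to day 28. Temperature, heart rate, respiratory rate and glucose are inputs to the sepsis criteria, and Table 1 places them on that schedule. Table 1 is not a full record of the criteria, because platelets, feed intolerance and culture results are absent from it. So the article does not settle whether sepsis on, say, day 20 would be ascertained or would count as an event.

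**The case against.** The strongest reply is that the article is silent and states no wrong rule. It nowhere says that already-septic patients stay in the later-day analyses. The over-time sentence is secondary, and the models it refers to are built on day 1 values, so it does not expressly say that later samples are scored. At-risk sets are commonly left to the full protocol or analysis plan, neither of which is shown. All of this is fair and limits the claim to a conditional one. It does not remove it. Using longitudinal data to follow model performance most naturally means scoring later samples, and the only outcome on offer is a grouping without dates. The septic versus non-septic longitudinal comparison is stated outright. Group curves are a legitimate description of the immune response over time, which is why onset alignment is proposed below as at least an added analysis.

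Two stronger readings are tempting.

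- A reader might infer that sepsis after day 14 is coded as non-septic. No section says so, and screening and cultures have no stated end. If such cases were missed and tested positive, specificity would fall. With 5% to 30% of the 132 missed and 90% of them test-positive, an assumed specificity of 0.70 would drop to between 0.66 and 0.51. For 10%: (88 × 0.70 + 13.2 × 0.10) / 101.2 = 0.62.
- A reader might also infer that day 1 is contaminated, since the Introduction says that "in response to a sterile insult, burns patients exhibit many of the classic diagnostic biomarkers of sepsis". But the criteria alone do not make a case. A positive culture or a response to antibiotics is also needed. The adult platelet criterion is not applied until three days after initial resuscitation, and feed intolerance is judged over more than 24 hours. Few patients could qualify at a sample taken within 24 hours of injury.

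**Conclusion.** The concern holds in conditional form. The plan tracks performance over time and compares septic with non-septic kinetics using a sepsis status that has neither onset nor window. If later samples are scored against that status, later-day accuracy is partly diagnostic and cannot be reported as prognostic. The septic curves pool pre-onset and post-onset samples in any case. The direction of the effect on sensitivity is upward as long as the marker detects established sepsis better than it predicts future sepsis. Its size cannot be derived from the documents, and the figures above rest on assumed onset shares and accuracies. The primary day 1 analysis is little affected by this.

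The mismatch between open-ended daily screening and data scheduled on days 1 to 14 and then day 28 is a separate clarification. It does bear on day 1 sensitivity and specificity, because it leaves their outcome window open. The documents do not support the statement that late cases are scored non-septic.

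**What to change.** 1. For each later-day performance analysis, include only patients alive and free of sepsis at that sample. Predict first onset after the sample over a stated horizon, of the same length for every day compared. A fixed calendar end would not do, since a day 14 end leaves 13 days from day 1 and none from day 14. Report the number of incident cases on each day.
2. In the kinetic models, separate pre-onset from post-onset samples by a time-varying sepsis status or by aligning samples to onset, at least as an added analysis beside the planned group comparison.
3. State until when sepsis is screened and recorded, and reconcile the Abstract with the data schedule and Table 1. Then set the outcome window for day 1 sensitivity and specificity to match that period. Cutting the primary outcome at day 14 by default should be avoided. It would turn later sepsis into a non-event and depart from the SIFTI-1 prevalence (35/57 = 61%, with no stated cut-off) behind the 60% assumption.

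The cost is mainly wording, with onset dates taken from the daily screen. The real price is precision on later days: if half of 132 cases are already septic, 66 incident cases remain and the exact interval at a sensitivity of 0.90 widens from 11 to 16 points. If the chosen window includes days 15 to 27, the onset data for those days must actually be recorded.
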